### Statistical methods and analysis

Our primary analyses will focus on the impact of active vs. sham stimulation (tVNS and CLAM-tACS) on neurobehavioral measures. To assess these effects, we will employ a linear mixed modelling approach to estimate the effects of treatment by time. Mediation will be assessed with path analyses.

First, we will investigate effects on cognitive function of augmented MBRP by administering the SGNG. Here, changes in SGNG behavioural inhibition pre to post treatment will be assessed, this further serves as a probe of the possible mediating effects of executive functioning on treatment success. We will further assess changes in cue reactivity as well as HDT interoceptive accuracy with multilevel modelling to allow for subject-specific effects [75]. Our study design also allows for the investigation of various levels of cue-induced effects, ranging from subjective indices of craving to physiological responses. Second, we will compare sham versus active stimulation + MBRP in terms of abstinence rates and drinking measures directly after and three months post treatment. We will investigate the course of clinical symptom severity as well as psychological measures before and after treatment as well as three months post treatment.

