## Methods and analysis

### Study design

We will conduct a four-arm randomized controlled study at the Department of Psychiatry and Neurosciences, Charité – Universitätsmedizin Berlin. Detoxified patients with Alcohol Use Disorder (AUD) will undergo a meticulously structured Mindfulness-Based Relapse Prevention (MBRP) program consisting of six weekly group sessions supplemented with daily individual mindfulness practice sessions. Prior to and following treatment, participants will undergo comprehensive assessments including cognitive control evaluation using a Simon Go/NoGo (SGNG) task, assessment of cue-induced craving and a heartbeat discrimination task (HDT) as a marker for interoception, complemented by electrocardiographic measurements of heart rate and heart rate variability, alongside 32-channel electroencephalography (EEG) recordings. The pre and post treatment assessments will encompass various clinical and psychological metrics, including symptom and craving severity, as well as perceived loneliness and impulsivity. Long-term treatment effects will be evaluated through a follow-up assessment after three months, focusing on abstinence rates and alcohol consumption (Fig. 1).

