### Inclusion criteria

ICD-10 diagnosis of alcohol dependence (F10.2) and at least 2 criteria for AUD according to DSM-5 (last 12 months).Completion of in-patient withdrawal treatment and abstinence duration less than 12 months.Ability to understand study information and provision of written informed consent.Age 18–70 years.

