### Psychophysiological data

#### Tasks

Before and after treatment we will assess cognitive control with a hybrid of the Simon and go/no-go paradigms (Simon go/no-go; SGNG) that has been shown to engage frontal midline regions [46, 64]. Furthermore, we will assess physiological cue reactivity with a passive viewing task that adheres to the guidelines provided by Ekhitiari et al. [65], along with measures of subjective cue-induced craving. Finally, to evaluate the effect of tVNS on interoceptive accuracy, participants will complete a heartbeat discrimination task (HDT) that is based on the one that was developed by Critchley et al. [66].

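### With only pre and post task measurements, the treatment-by-time mixed model on its ordinary reading is a change-score comparison; adjusting for the pre value gives a more precise contrast at almost no cost.

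*Protocol article*

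**What the plan says.** Statistical methods and analysis sets the primary aim: "Our primary analyses will focus on the impact of active vs. sham stimulation (tVNS and CLAM-tACS) on neurobehavioral measures". For this, "we will employ a linear mixed modelling approach to estimate the effects of treatment by time". On the inhibition task it adds that "changes in SGNG behavioural inhibition pre to post treatment will be assessed". Cue reactivity and heartbeat-discrimination accuracy are also described as changes, to be analysed "with multilevel modelling to allow for subject-specific effects".

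The schedule gives two occasions for these measures. Study design: "Prior to and following treatment, participants will undergo comprehensive assessments". Tasks: "Before and after treatment we will assess cognitive control with a hybrid of the Simon and go/no-go paradigms", with the cue-reactivity and heartbeat tasks described in the same paragraph. The three-month visit serves abstinence and drinking (Study design; Clinical measures). Only the clinical and psychological measures are to be followed "before and after treatment as well as three months post treatment".

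The article does not list the fixed effects. It does not say whether the arms may differ at baseline in the model, and it neither mentions nor excludes the pre value as a covariate.

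**The concern.** With two occasions, everything turns on how the model treats the pre-treatment measurement. If each arm has its own free baseline mean, the treatment-by-time term subtracts the whole observed baseline difference from the post difference. Under randomisation that baseline difference is chance alone, and the best prediction of its carry-over to post is only a fraction ρ of it (for equal variances). Subtracting all of it over-corrects and adds noise.

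What is at stake is efficiency, not validity. Averaged over randomisation the change-score contrast is unbiased, but it spends patients to reach a precision that the data already collected could give. In a single trial, the two analyses can also give visibly different answers if the arms differ at baseline by chance. That is a reason to fix the choice before the data are seen.

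**Working it through.** **Inputs.** From the article: two occasions for the tasks (Study design; Tasks), a treatment-by-time mixed model (Statistical methods and analysis), and 20 per CLAM-tACS group (Sample size). Assumed, because the article does not give them: the pre-post correlation ρ, shown from 0.3 to 0.9; equal variance σ² at pre and post; and, for the power illustration, a true effect of 0.8 in units of σ. The article states no figure for the precision of this model, so there is none to reproduce.

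**Step 1: what the interaction estimates.** With arm, time and arm-by-time as fixed effects, a random subject intercept and complete pairs, the interaction is (post − pre) in the active arm minus (post − pre) in the sham arm. A simulation with 20 per arm (150 data sets at each of ρ = 0.3, 0.5 and 0.7) confirmed it: the mixed-model interaction and the change-score difference agreed to about 2 × 10⁻¹⁵. The subject-specific intercept therefore does not amount to baseline adjustment.

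**Step 2: variances.** Per patient, in units of σ²:
- change score: 1 + 1 − 2ρ = 2(1 − ρ)
- adjusted for the pre value, or with baseline means constrained equal: 1 − ρ²
- ratio: (1 − ρ)(1 + ρ) / [2(1 − ρ)] = (1 + ρ)/2

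| Assumed ρ | Change score | Adjusted | Ratio |
|---|---|---|---|
| 0.3 | 1.40 | 0.91 | 0.65 |
| 0.5 | 1.00 | 0.75 | 0.75 |
| 0.7 | 0.60 | 0.51 | 0.85 |
| 0.9 | 0.20 | 0.19 | 0.95 |

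The number of patients cancels from the ratio. At ρ = 0.5, a change-score analysis needs 20/0.75 ≈ 27 per arm to match 20 per arm with adjustment.

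**Step 3: simulated spread of the estimate, 20 per arm.**

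| Assumed ρ | Unconstrained mixed model = change score | Constrained mixed model | Pre value as covariate |
|---|---|---|---|
| 0.3 | 0.339 | 0.286 | 0.287 |
| 0.5 | 0.296 | 0.264 | 0.266 |
| 0.7 | 0.252 | 0.220 | 0.222 |

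The two remedies are equivalent in precision, and both beat the unconstrained model.

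**Step 4: illustration in power.** Two-sided 0.05, noncentral t, 20 per arm, assumed effect 0.8. The standardised effect is 0.8/√[2(1 − ρ)] with 2n − 2 = 38 degrees of freedom for the change score, and 0.8/√(1 − ρ²) with 2n − 3 = 37 for the adjusted contrast.

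| Assumed ρ | Standardised effect, change → adjusted | Power, change → adjusted |
|---|---|---|
| 0.3 | 0.676 → 0.839 | 0.55 → 0.73 |
| 0.5 | 0.800 → 0.924 | 0.69 → 0.81 |
| 0.7 | 1.033 → 1.120 | 0.89 → 0.93 |

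**Step 5: does the gain depend on arm size?** Hold the effect at 0.577 in change-score SD units (the value the article quotes as dz, used here only as a common yardstick) and ρ at 0.5. Power then moves from 42.8% to 53.7% with 20 per arm (+10.9 points), from 72.2% to 83.7% with 40 (+11.5) and from 81.5% to 91.0% with 50 (+9.5). The gain is about the same throughout.

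**The case against.** The strongest reply is that the article does not specify the model being criticised. A mixed model with equal baseline means also contains a treatment-by-time term, so the quoted sentence is compatible with the better analysis. Parametrisation and covariates are commonly left to the full protocol or the SAP, neither of which is shown. Speaking of change from pre to post may describe the question and not the estimator. This stands as far as it goes: no error is proven. But the wording leads most naturally to the unconstrained interaction, and settling it takes one sentence.

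Second, the exact equality needs complete pairs. With dropout, a likelihood-based model also uses patients seen only at baseline and no longer equals the observed change-score difference. That is correct, but a free baseline arm difference is still subtracted in full, so the inefficiency remains.

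Third, if the tasks are highly repeatable the benefit is small: 5% of the variance at ρ = 0.9. This also stands.

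Two stronger readings should not be drawn:
- A reader might infer that the loss matters most in the small CLAM-tACS arms. The variance ratio is the same at any size and the power gain is not larger there. Only the likely size of a chance baseline imbalance grows as arms shrink. Nor should the 20% attrition be used to reduce those arms further, since Sample size states it for tVNS only.
- Because entry requires "Completion of in-patient withdrawal treatment and abstinence duration less than 12 months", a reader might infer that entry abstinence is wrongly left out of the drinking analyses. That rests on silence in a condensed article, and the article gives no figure for its prognostic value.

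**Conclusion.** The point holds as an efficiency improvement. On the ordinary reading of the planned model, the task outcomes would be compared by difference in mean change. That comparison is valid, but its variance is 2/(1+ρ) times that of a baseline-adjusted contrast. Adjustment brings the variance to between 0.65 and 0.95 of the change-score value for ρ from 0.3 to 0.9, in the tVNS and CLAM-tACS comparisons alike.

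The result rests on an assumed ρ, equal variances at pre and post, complete pairs for the exact identity, and a model with a free baseline arm effect. The power figures also rest on an assumed effect of 0.8 and illustrate the gain; they do not forecast this trial's power. The point concerns the measures taken at two occasions; the identity does not carry over in this form to those also taken at three months.

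**What to change.** Add one sentence to Statistical methods and analysis. Either keep the mixed model and constrain the pre-treatment means to be equal across the randomised arms, with treatment effects entering only after baseline, or model the post value with the pre value as a covariate. In both cases, name the active-versus-sham contrast at post as the estimate for the inhibition, cue-reactivity and heartbeat measures. If the full protocol or SAP already says this, the article only needs to repeat it.

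The change uses data already being collected, adds no visit or patient, and costs at most one degree of freedom. It should be settled before any unblinded analysis, so that nobody chooses between the two estimators after seeing the results.

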### Patient and public involvement

The feedback of a committee that consists of affected AUD patients and the Federal Association of the Families of Mentally ill People as well as speakers of addiction counseling centers in Berlin has been incorporated in the design of this study. In addition, we will collect feedback from all participating AUD patients at the end of their participation. This allowed us to adapt the design of the current study as closely as possible to the needs of those affected and to take experience gained from participating in our study into account for future projects.

## Discussion

This research project endeavors to enhance the effectiveness of MBRP while advancing treatment options for AUD. The study will delve into the nuanced impact and underlying mechanisms of neurostimulation protocols in conjunction with MBRP. Specifically, we will investigate the potential of tVNS and CLAM-tACS as supplementary treatments without incorporating a control intervention to MBRP. Numerous meta-analyses have highlighted the effectiveness of various mindfulness-based interventions (MBIs) in AUD populations, prompting our exploration into the mechanisms underlying this efficacy [76, 77]. While our study design does not allow for conclusive findings regarding potential disparities in cue reactivity, cognitive control, and interoceptive abilities between AUD individuals and healthy controls, we aim to monitor the potential influence of our intervention on these factors. Additionally, we anticipate that disease severity and treatment efficacy could be predicted based on these factors and their interplay, considering the inherent heterogeneity within AUD populations [78]. Conducting exploratory analyses on individual profiles could significantly contribute to a dimensional conceptualization, thereby facilitating the development of enhanced treatment and prevention strategies.

## Data Availability

No datasets were generated or analysed during the current study.

## Abbreviations

ACC: Anterior Cingulate Cortex
AASE: Abstinence Self–Efficacy Scale
ADS: Alcohol Dependence Scale
AUD: Alcohol Use Disorder
AUQ: Alcohol Urge Questionnaire
BIS-15: Barratt Impulsiveness Scale–15
CLAM-tACS: Closed–Loop Amplitude–Modulated Transcranial Alternating Current Stimulation
DSM-5: Diagnostic and Statistical Manual of Mental Disorders, 5th Edition
EEG: Electroencephalography
FMΘ: Frontal Midline Theta
FFA: Freiburg Mindfulness Inventory (FFI; German: Freiburger Fragebogen zur Achtsamkeit)
FFMQ: Five Facet Mindfulness Questionnaire
GCP: Good Clinical Practice
GDPR: General Data Protection Regulation
HDT: Heartbeat Detection Task
ICD-10: International Classification of Diseases, 10th Revision
MBRP: Mindfulness–Based Relapse Prevention
MBSR: Mindfulness–Based Stress Reduction
MBCT: Mindfulness–Based Cognitive Therapy
MBIs: Mindfulness–Based Interventions
M-CIDI: Munich Composite International Diagnostic Interview
OCDS: Obsessive Compulsive Drinking Scale
PANAS: Positive and Negative Affect Schedule
PFC: Prefrontal Cortex
PSS: 10–Perceived Stress Scale–10
PsyFlex: Psychological Flexibility Questionnaire
SCID-5: Structured Clinical Interview for DSM–5
SGNG: Simon Go/No–Go task
STAI: State–Trait Anxiety Inventory
TICS: Trier Inventory for Chronic Stress
TMS: Transcranial Magnetic Stimulation
tVNS: Transcutaneous Vagus Nerve Stimulation
URICA: University of Rhode Island Change Assessment
VS: Ventral Striatum
